#### Secondary Outcomes

Some of the symptoms associated with essential hypertension, such as vertigo, headache, and insomnia, will be assessed using scales such as the Dizziness Handicap Inventory (DHI), Headache Impact Test-6 (HIT-6), and the Pittsburgh Sleep Quality Index (PSQI). The DHI is a classic tool for assessing vestibular or dizziness-related dysfunction and contains 25 entries covering functional, affective, and somatic dimensions [40]. In hypertensive patients, dizziness is a common symptom that may be associated with blood pressure fluctuations or medication side effects. The HIT-6 is a 6-item questionnaire that assesses the impact of headache on daily functioning in patients with hypertension associated with headache (eg, migraines or medication-induced headache) [41]. The PSQI is a 19-item tool that assesses sleep disorders, which are often comorbid in patients with hypertension (eg, insomnia and sleep apnea) [42,43].

The above assessments will be performed at baseline, at week 6 of starting treatment, and at weeks 1, 2, and 4 after the end of treatment. In addition, other safety indicators will be assessed, including general physical examination, liver and renal function and electrocardiogram at baseline. These tests will be performed at baseline and at week 6 of treatment.

#### Follow-Up

Telephone follow-ups will be conducted at weeks 1, 2, and 4 after the completion of acupuncture treatment. Patients will record their home self-measured blood pressure values, medication intake, and related scale contents accurately and completely in the case report form (CRF). The researcher will provide professional guidance to the patients according to their blood pressure level and related accompanying symptoms.

#### Sample Size and Statistical Analysis

The sample size of this study was estimated using the 2-sample *t* test in PASS (Power Analysis and Sample Size Software; NCSS LLC) 11 efficacy. According to existing literature [44], the mean improvement in systolic blood pressure within 24 hours for patients with essential hypertension treated with acupuncture was 8.9 mm Hg, while the mean improvement for those treated with sham acupuncture was 5.4 mm Hg, resulting in a clinical effect difference of 3.5 mm Hg. The SD for each group was 9.9 mm Hg. The sample size calculation assumed a 2-tailed significance level (α) of 0.05 and a statistical power (1-β) of 80%, the total sample size required for acupuncture treatment of mild-to-moderate essential hypertension was calculated to be 102 cases. Accounting for a 10% dropout rate, a total of 228 hypertensive participants needed to be recruited, with 114 participants in each group.

Statistical analyses we will leave to a statistician who is unaware of the groups. Data will be analyzed using the SAS 9.3 and SPSS 29.0 (IBM Corp) packages, and a 2-sided *P*<.05 will be considered statistically significant. We will use the intention-to-treat analysis set for outcome analysis and also validate it using per-protocol analysis to determine if the two results are consistent and inconsistency will require further analysis and discussion. For patients who withdrew from the study midway through the study, baseline data and follow-up data that had been collected before withdrawal were included in the intention-to-treat analysis. Missing values will be interpolated by the last observation carried forward method.

Baseline data on participants’ demographic information and general state characteristics such as age, gender, and disease duration will be represented by descriptive statistics for both groups. We will measure in-office immediate blood pressure values at different time points of the needle prick and 24-hour ambulatory blood pressure values at baseline, week 6 of treatment and week 4 after the end of treatment, and comparisons between groups will be assessed using repeated measures ANOVA.

For continuous variables, expressed as mean (SD), grouped *t* tests will be used if they conform to normal distribution and vice versa, that is, they will be assessed by Wilcoxon rank-sum test; categorical variables will be compared using chi-square test or Fisher exact test (Fisher), and the results of the data will be documented in the form of percentage.

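### The printed inputs require 127 evaluable participants per group, not 102; at 102 per group the power is about 71% rather than 80%, and 102 is wrongly labelled a total

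*Protocol article*

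**What the plan says.** Everything is in the protocol article, under Sample Size and Statistical Analysis.

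- Method: "The sample size of this study was estimated using the 2-sample *t* test in PASS".
- Effect: the mean fall in 24-hour systolic pressure "treated with acupuncture was 8.9 mm Hg", and "the mean improvement for those treated with sham acupuncture was 5.4 mm Hg", "resulting in a clinical effect difference of 3.5 mm Hg".
- Variability: "The SD for each group was 9.9 mm Hg".
- Error rates: "The sample size calculation assumed a 2-tailed significance level (α) of 0.05", with power set at 80%.
- Result: "the total sample size required for acupuncture treatment of mild-to-moderate essential hypertension was calculated to be 102 cases".
- After an allowance of 10% for dropout: "a total of 228 hypertensive participants needed to be recruited, with 114 participants in each group".

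The section headed Randomization gives 1:1 allocation. The Abstract and Study Design repeat 228 as the enrolment target.

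**The concern.** The paragraph gives every input that a two-sample t test calculation needs, so the result can be checked without any assumption. Two things do not fit. First, 102 is too small for a standardised difference of 3.5/9.9 = 0.354 at two-sided 0.05 and 80% power. Second, 102 is called the total, while the next sentence recruits 114 in each group.

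The stated power is what ethics reviewers and readers use to judge whether 228 participants are enough. If it is overstated, the chance of missing the planning effect is larger than declared, and a non-significant result would be read as stronger evidence against the treatment than it is.

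**Working it through.** **Inputs, all from the sample size paragraph except allocation (Randomization):** difference 8.9 − 5.4 = 3.5 mm Hg; SD 9.9 mm Hg per group; two-sided alpha 0.05; power 80%; 1:1 allocation; dropout 10%.

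**1. The plan's own dropout step.** 102/(1 − 0.10) = 113.3, rounded up to 114; 2 × 114 = 228. This reproduces the recruitment target, but only with 102 as the number per group. If 102 were the total, the same step would give 114 recruited in all, not 228.

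**2. Required n from the printed inputs.** By the normal approximation,

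n per group = 2 (1.960 + 0.842)² × 9.9² / 3.5² = 125.6, rounded up to 126.

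The exact calculation for the t test (noncentral t) gives 126.6, rounded up to 127 per group, or 254 evaluable in total. With 10% dropout, 127/0.9 = 141.1, rounded up to 142 per group, or 284 in total. The printed 102 is about 20% below 127 (25/127), which rounding cannot explain.

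**3. Power at the planned sizes** (two-sample t test, difference 3.5, SD 9.9, two-sided 0.05):

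| Evaluable per group | Power | Difference detectable with 80% power |
|---|---|---|
| 102 | 71.0% | 3.90 mm Hg |
| 114 (no dropout) | 75.7% | 3.69 mm Hg |
| 127 | 80.1% | 3.49 mm Hg |

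Read literally, a total of 102 means 51 per group, with power 42.4%. Step 1 shows that this reading is not intended.

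**4. What would give about 102 per group.** Each route contradicts something printed:

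| Change to one input | n per group (t test) |
|---|---|
| SD 8.9 instead of 9.9 | 102.5 (normal approximation 102) |
| Difference about 3.9 instead of 3.5, SD 9.9 | about 102 |
| One-sided alpha 0.05 | 99.6, rounded up to 100 |

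The one-sided route comes close but does not give 102, and the text says 2-tailed. The document does not show which of these, if any, occurred.

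**The case against.** The arithmetic itself is hard to dispute: all inputs are printed and nothing elsewhere in the article corrects the result. The best case on the other side is about what follows from it.

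*The label total is a slip that the paragraph resolves itself.* This is fair. The next sentence gives 114 per group and 228 overall, so nobody would recruit 102 in all, and the 42% figure should carry no weight. The wording still needs correcting.

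*The 71% is the power of a t test, whereas blood pressure will be compared by repeated measures ANOVA.* This stands as a limit on the claim. The power of that analysis depends on correlations the article does not give. But the article bases its 80% on the t test and claims no gain from repeated measures, so the stated justification fails on its own terms. A baseline-adjusted analysis could recover the loss. If 9.9 is the SD of change and the variances at baseline and week 6 are equal, adjustment multiplies the variance by (1 + ρ)/2, where ρ is the correlation between baseline and week 6. Power at 102 per group is then 82.7% at ρ = 0.5, 80.2% at 0.6, 77.8% at 0.7 and 75.4% at 0.8. None of these conditions is stated in the article, and it does not specify such an analysis, so this cannot rescue the printed figure.

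*The SD may simply be misprinted.* It may be: about 8.9 would make 102 correct. The SD comes from a cited study that cannot be checked here, and solving backwards for one input will always find some value. This is a reason to look up the PASS run before restating the power. It does not defend the text as printed.

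*Quoting 3.9 mm Hg fits the target to the sample size.* This is also fair. The article gives no clinical basis for 3.9, so it should be described only as what 102 per group can detect.

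**Conclusion.** The concern holds. On the article's own inputs the trial needs 127 evaluable per group for 80% power. The planned 102 gives 71.0%, a shortfall of 9 percentage points, so the chance of missing a true 3.5 mm Hg difference is 29% instead of 20%. Full retention of all 228 participants would still give only 75.7%. The label total on 102 contradicts the recruitment figures and should read per group.

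This rests on the printed difference, SD, alpha and test being those intended. If one is a misprint, the sample size may be right and the text wrong; either way the paragraph is incorrect as it stands. The cause is not known, and the power of the planned repeated measures analysis cannot be worked out from the article.

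**What to change.** 1. Retrieve the PASS run and compare its inputs with the paragraph. If it used a different SD, difference or sidedness, print the values actually used and their source.
2. Replace the total of 102 with 102 evaluable per group (204 in total), leading to 114 per group (228) after 10% dropout.
3. If the printed inputs are confirmed, restate the power as about 71% for 3.5 mm Hg with SD 9.9, and add that 102 per group gives 80% power for 3.9 mm Hg, without presenting 3.9 as the planning effect.
4. If the sponsor wants to rely on baseline adjustment to reach 80%, the adjusted analysis must be specified, and the correlation and the meaning of the SD stated, with a range such as the one shown above.

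Steps 1 to 3 change wording in the protocol and the registry entry only. They add no participants; the price is a less favourable power statement. If the sponsor would rather keep 80% for 3.5 mm Hg under the t test, the target becomes 142 per group (284 in total), which is 56 more than planned. The article reports 27 recruited and no data analysed, so either course could be taken, at that stage, before any results were known.

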This study aims to conduct a multicenter randomized controlled trial to evaluate the efficacy and safety of the “HuoXueSanFeng” acupuncture technique in managing essential hypertension. The primary objective is to assess the onset and duration of the blood pressure–lowering effects of acupuncture.

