### Outcome Measurements

#### Primary Outcome Measurement

In this study, the assessor will be blinded to the specific subgroups. The primary outcome will include 24-hour ambulatory blood pressure and in-office immediate blood pressure. We plan to measure 24-hour ambulatory blood pressure once at baseline, once a week 6 of treatment, and once a week 4 after the end of treatment. In-office blood pressure will be measured when the patient first arrives at the office, 5 minutes after lying down, and at 5, 15, and 30 minutes after completing the acupuncture operation and 10 minutes after finishing the needle.

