#### Data Management and Quality Control

A thorough assessment will be performed during the screening and preparation phase of the trial and periodically throughout the trial. The screening phase will last for 1 week and will include assessment of basic information such as gender, age, temperature, heart rate, respiration, BMI, etc, as well as detailed information about the participant's chief complaint, current medical history, past history, family history, routine checkups, blood pressure, and medication use. The timing and process of data collection are detailed in Table 3.

Before the formal commencement of the study, all researchers will undergo a uniform and rigorous training to ensure that they are familiar with and equipped with the diagnostic and therapeutic measures and basic assessment skills to improve the consistency of internal observations. According to the study protocol, we will collect complete and authentic raw data from the participants and keep detailed records. Any data that deviate significantly from the clinically acceptable range must be examined and interpreted. The completed and validated CRF will be given to the relevant personnel for data entry, management and statistics, and the data on the CRF will not be modified. Professionals will be assigned to provide regular supervision and quality control throughout the study.

**Table 3 table3:** Clinical research flowchart.

Phase project	Baseline period	On-treatment			Follow-up period		
	Week 0	Week 1	Week 6	Week 7		Week 8	Week 10
Signed informed consent	✓^a^						
Filling in demographic information	✓						
Previous diseases and medication	✓						
Prestudy medication and other treatments	✓						
General physical examination items	✓						
Physical examination	✓						
Acceptance and discharge standard	✓						
24-hour ambulatory blood pressure monitoring	✓		✓				✓
Immediate blood pressure in the consulting room^b^		✓	✓				
Biochemical function test^c^	✓		✓				
Electrocardiogram	✓		✓				
Scale evaluation^d^	✓		✓	✓		✓	✓
Blinded evaluation			✓				
Adverse reactions/adverse events (ADR/AE)	✓^e^	✓^e^	✓^e^	✓^e^		✓^e^	✓^e^
New drug combinations	✓^e^	✓^e^	✓^e^	✓^e^		✓^e^	✓^e^

^a^“✓” in this table represents the items that must be completed; The participants made corresponding records after treatment.

^b^Immediate blood pressure in the consulting room: it needs to be measured in the first to sixth weeks.

^c^Biochemical function test: liver function, kidney function, blood lipid, etc.

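### LOCF is a poor fit to 24-hour ambulatory BP measured at only three visits: modest attenuation at the planned equal 10% loss, and bias in either direction if loss differs by arm or the effect wanes

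*Protocol article*

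**What the plan says.** The statistical paragraph (Methods, Sample Size and Statistical Analysis) states one rule for missing data: "Missing values will be interpolated by the last observation carried forward method". It applies to the intention-to-treat analysis, where for people who withdraw "baseline data and follow-up data that had been collected before withdrawal were included in the intention-to-treat analysis". The between-group method for BP is given as "comparisons between groups will be assessed using repeated measures ANOVA". A per-protocol analysis is planned as a consistency check. No other missing-data method or missing-data sensitivity analysis is stated.

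Under Primary Outcome Measurement, "The primary outcome will include 24-hour ambulatory blood pressure and in-office immediate blood pressure". Ambulatory BP is taken "once at baseline, once a week 6 of treatment, and once a week 4 after the end of treatment", and Table 3 places these readings at weeks 0, 6 and 10. For in-office BP, a footnote to Table 3 says "it needs to be measured in the first to sixth weeks", with no reading during follow-up.

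The Introduction makes timing central: "The primary objective is to assess the onset and duration of the blood" pressure–lowering effect. Week 10 is the only ambulatory reading after treatment ends. The Follow-Up section describes the contacts in that period as remote: "Telephone follow-ups will be conducted at weeks 1, 2, and 4 after the completion of acupuncture treatment".

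**The concern.** Ambulatory BP is a primary outcome and the basis of the sample size. With three readings, LOCF has very little to carry.

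- **Week 6 missing.** The only earlier value is the baseline, so the imputed change is exactly zero. The plan itself expects mean falls of 8.9 mm Hg (acupuncture) and 5.4 mm Hg (sham), so the imputed value contradicts its own assumption in both arms.
- **Week 10 missing, week 6 present.** The end-of-treatment value is entered at a visit four weeks after treatment. For these participants the analysis assumes that the effect lasts, and duration is what the trial sets out to measure.
- **Both missing.** The baseline is carried to week 10 as well, which works against persistence.

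At stake are the size of the week-6 contrast, its error rate if the arms lose different shares of participants, and the credibility of the duration result.

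**Working it through.** **Inputs from Sample Size and Statistical Analysis:** falls of 8.9 and 5.4 mm Hg, difference 3.5, SD 9.9 per group, two-sided α 0.05, 114 per group, 10% dropout. I take 9.9 as the SD of the change.

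**Assumptions, not in the document:** how dropout splits by arm, when it occurs, how much of the effect remains at week 10, and that dropout is unrelated to outcome.

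**The plan's own figure.** 102/0.9 = 113.3, rounded up to 114 per group, so the dropout step reproduces if 102 is per group. The 102 itself does not follow from the stated inputs (126 to 127 per group for 80% power). That is a separate matter, but it explains why the power figures below start near 72%.

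**Week 6, planned effects.** With dropout shares dA (acupuncture) and dS (sham) before week 6:

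LOCF contrast = 8.9(1 − dA) − 5.4(1 − dS)

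Variance in an arm with mean fall c and loss d = (1 − d) × 9.9² + d(1 − d)c²

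| dA / dS | LOCF contrast | Bias against 3.5 |
|---|---|---|
| 5% / 5% | 3.325 | −0.175 |
| 10% / 10% | 8.01 − 4.86 = 3.15 | −0.35 |
| 20% / 20% | 2.80 | −0.70 |
| 5% / 15% | 8.455 − 4.59 = 3.865 | +0.365 |
| 15% / 5% | 7.565 − 5.13 = 2.435 | −1.065 |

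Power at 10% / 10%: the variances are 95.34 and 90.83, so SE = √((95.34 + 90.83)/114) = 1.278. Then 3.15/1.278 = 2.465, giving power of about 69%. Without LOCF, with 114 × 0.9 = 102.6 observed per group, SE = 9.9 × √(2/102.6) = 1.382. Then 3.5/1.382 = 2.532, giving about 72%.

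**Week 6, no true difference.** Both arms truly fall by c, so the spurious difference is c × |dS − dA|:

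| Loss by arm | c = 5.4 | c = 8.9 |
|---|---|---|
| 10% vs 10% | 0; type I error 5.0% | 0; 5.0% |
| 8% vs 12% | 0.216, SE 1.262; 5.3% | 0.356, SE 1.293; 5.9% |
| 5% vs 15% | 0.54, SE 1.262; 7.1% | 0.89, SE 1.292; 10.6% |

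**Week 10.** Loss d occurs only after week 6 and is equal in both arms. A share r of the effect is retained:

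LOCF contrast = (1 − d) × r × 3.5 + d × 3.5

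- r = 0, d = 10%: 0.35 against a true 0. With SE of about 1.31 (9.9 × √(2/114)), rejection is about 5.8%.
- r = 0.5, d = 10%: 1.575 + 0.35 = 1.925 against a true 1.75.
- r = 1: 3.5 against 3.5, no bias.

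With unequal late loss and half of each arm's fall retained, the result can fall on either side of 1.75: 2.28 at 15% / 5% and 1.57 at 5% / 15%.

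The week-6 and week-10 examples each spend the whole 10%, so they are alternatives and must not be added.

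**The case against.** The strongest reply is that, at the one dropout figure the plan gives, little happens. Equal 10% loss pulls the contrast toward zero, creates no false positives and costs about 2 to 3 points of power. Most of the shortfall from 80% comes from the sample-size calculation. This stands, and it limits how serious the point is.

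A reader might infer that LOCF raises the false-positive rate to 7–11%. The documents do not support that as an expectation. It needs a threefold imbalance in loss, for which they give no figure, and the upper end also needs sham to fall by 8.9 rather than the planned 5.4. At 8% versus 12% the rate is 5.3–5.9%. Imbalance is not far-fetched, since only the active needles penetrate the skin, but it remains an assumption.

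A reader might also infer that LOCF always builds persistence into the duration result. It does not: the bias is zero if the effect is fully retained, and early leavers carry their baseline forward.

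Nor does the zero-change mechanism extend to in-office BP, where LOCF carries a reading from weeks 1 to 6.

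The per-protocol comparison gives some protection, because early withdrawals would normally be left out of it. But it changes the population and does not test the missing-data assumption, so it does not answer the point.

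**Conclusion.** The point holds for 24-hour ambulatory BP and should be fixed. The stated rule imposes zero change at week 6 and, where week 6 is present, an on-treatment value at week 10. The three-visit schedule makes both consequences unavoidable whenever those readings are missing.

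At the planned loss, split equally, the cost is 0.35 mm Hg, or 10% of the target difference, with the error rate intact. The larger consequences are conditional: unequal loss for direction and type I error, and a waning effect for overstated persistence. Because the direction depends on which arm loses more participants, LOCF cannot be defended as conservative. The telephone format described for the week-10 contact, when ambulatory monitoring is also due, may make missing week-10 readings more common, but the documents give no rate.

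**What to change.** For ambulatory BP, replace LOCF and the repeated measures ANOVA with a likelihood-based repeated-measures model on all observed values at baseline, week 6 and week 10. Treat baseline as part of the response vector, with its mean constrained equal across arms, an unstructured covariance, and terms for centre, visit and group-by-visit. If baseline were only a covariate, anyone leaving before week 6 would have no outcome row and would drop out of the model, although the plan keeps their baseline data in the intention-to-treat analysis.

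The model rests on data being missing at random, so add one multiple-imputation sensitivity analysis under a missing-not-at-random shift.

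This recommendation does not cover in-office readings.

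The cost is one paragraph of analysis text and slightly more programming in the SAS package already named, with no new data. The article reports 27 participants recruited and no analysis done, so at that stage the change can still be pre-specified.

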### Randomization and Assignment Hiding

#### Randomization

Randomization will be performed using stratified block randomization. Randomization will be performed by a statistician not involved in trial implementation or statistical analysis, and random sequences will be generated using the Proc plan program in SAS 9.3 software (SAS Institute). Eligible participants will be randomized in a 1:1 ratio into a needling group and a sham needling group. Stratification by center factor will be applied, with block sizes of 4 or 6.

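### The repeated-measures ANOVA of 24-hour blood pressure lists baseline with the outcome visits, names no tested term and does not adjust for baseline, so it does not match the comparison the trial was sized on

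*Protocol article*

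**What the plan says.** All of this is in the protocol article.

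- **Analysis** (Sample Size and Statistical Analysis). The ambulatory values are listed as "24-hour ambulatory blood pressure values at baseline, week 6 of treatment and week 4 after the end of treatment, and comparisons between groups", and "comparisons between groups will be assessed using repeated measures ANOVA". The text does not say whether the group main effect, the group-by-time interaction or a contrast at one visit is the test. No baseline adjustment is mentioned.
- **Sample size** (same section). The basis is a two-sample t test on mean improvement in 24-hour systolic pressure, 8.9 against 5.4 mm Hg, "resulting in a clinical effect difference of 3.5 mm Hg". It adds "The SD for each group was 9.9 mm Hg", with a "2-tailed significance level (α) of 0.05 and a statistical power (1-β) of 80" percent. No visit is named.
- **Randomization**. "Stratification by center factor will be applied, with block sizes of 4 or 6". The analysis text neither includes nor excludes centre.
- **Introduction**. The primary objective concerns when the pressure-lowering effect begins and how long it lasts.

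**The concern.** Before treatment, randomised groups differ only by chance, so a baseline reading carries no information about the treatment effect except as a covariate. Entered as one of three outcome levels, it leaves two candidate tests, and neither is the comparison that was powered.

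- The **group main effect** averages a visit with zero expected difference together with the two visits that matter.
- The **group-by-time interaction** asks whether the group difference varies over the three visits. A significant result does not say at which visit the groups differ, or by how much.

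An objective about onset and duration needs a difference at each post-treatment visit. Efficiency also matters, because the plan's own two-sided inputs give less than the 80% power it claims.

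**Working it through.** **Inputs from the article:** difference 3.5 mm Hg; SD 9.9; two-sided alpha 0.05; 102 before dropout; 114 per arm recruited; ambulatory readings at baseline, week 6 and week 4 after treatment.

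**Assumptions, not in the article:** 9.9 is the SD of the improvement (the quoted means are improvements); compound symmetry with correlation ρ from 0.3 to 0.8; centre explains 0 to 10% of the variance. Holding the SD of change at 9.9 gives a single-visit variance σ² = 9.9² / [2(1−ρ)].

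**1. The plan's own figure.** n per arm = 2(1.96 + 0.84)² × 9.9² / 3.5² ≈ 126 (127 by t test), not 102. A one-sided test would need 99 (100 by t test), but the text says 2-tailed. The article says "the total sample size required for acupuncture treatment of mild-to-moderate essential hypertension was calculated to be 102 cases", yet only 102 per arm leads to the stated recruitment: 102 / 0.9 = 113.3, so 114 per arm and 228 in total. I therefore use 102 per arm. The sample-size discrepancy is a separate matter.

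**2. Unadjusted change.** SE = 9.9 × √(2/102) = 1.386; 3.5 / 1.386 = 2.52; power 71% (76% at 114 per arm).

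**3. Group main effect with baseline as a level.** Estimate = (0 + 3.5 + 3.5)/3 = 2.33 mm Hg if the effect persists. Variance of a participant's three-visit mean = σ²(1 + 2ρ)/3. At ρ = 0.5: σ² = 98.01, variance 65.34, SE = √(65.34 × 2/102) = 1.13, ratio 2.06, power 54%. If half the effect persists, the estimate is (0 + 3.5 + 1.75)/3 = 1.75 mm Hg.

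**4. Group-by-time, 2 df.** Noncentrality = (n/2) Σ(d − d̄)² / [σ²(1−ρ)], where σ²(1−ρ) = 9.9²/2 = 49.0, so ρ cancels.
- Effect persists: 51 × 8.17 / 49.0 = 8.50; power 74%.
- Half persists: 51 × 6.125 / 49.0 = 6.37; power 61%.

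**5. ANCOVA at week 6.** Residual variance = σ²(1−ρ²) = 9.9²(1+ρ)/2. At ρ = 0.5: 73.5, SE = √(73.5 × 2/102) = 1.20, ratio 2.92, power 83%.

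Power at 102 per arm:

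| ρ | Main effect, persists | Main effect, half persists | Group-by-time, persists / half | Unadjusted change, week 6 | ANCOVA, week 6 |
|---|---|---|---|---|---|
| 0.3 | 78% | 53% | 74% / 61% | 71% | 88% |
| 0.5 | 54% | 34% | 74% / 61% | 71% | 83% |
| 0.7 | 31% | 19% | 74% / 61% | 71% | 78% |
| 0.8 | 21% | 14% | 74% / 61% | 71% | 75% |

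At 114 per arm, over ρ = 0.3 to 0.8, the main effect (persisting) has 82% to 23%, group-by-time 79% (66% if half persists), unadjusted change 76%, and ANCOVA 91% to 80%.

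**6. Centre.** If a share c of the variance lies between centres, the true SE is 9.9 × √[(1−c) × 2/102], while the unadjusted test uses 9.9 × √(2/102). For c = 0, 5% and 10%, unadjusted against adjusted power is 71/71%, 72/74% and 72/76%. Unadjusted type I error is 0.050, 0.044 and 0.039.

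**The case against.** **Dilution is not established.** A reader might infer that the plan shrinks the effect by a third. The article does not support that as fact: it names no term, and group-by-time, the usual term of interest when baseline is a level, is not diluted. This stands. The shrinkage is conditional, and the unnamed term is the defect.

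**The power loss may be modest.** Group-by-time at 74% slightly exceeds the 71% of the t test on change. With a persisting effect, ANCOVA gains only 4 points over it at ρ = 0.7 and 1 point at ρ = 0.8. At ρ = 0.3 even the diluted main effect, at 78%, beats the unadjusted change. All this stands, and no single correlation should carry the argument. It does not rescue the interaction as an estimate of the effect.

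**Visit contrasts can follow an ANOVA.** They can, and a multi-visit analysis suits the objective. But none is named, and contrasts of raw values would still lack baseline adjustment. The sample size names no week either, so making week 6 primary is a choice, though a natural one as the end of treatment.

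**Centre.** A reader might infer that the analysis leaves out the stratification factor. Silence in a condensed article is not exclusion, and covariates are commonly left to the fuller documents. Centre belongs in the fix only.

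**The symptom scales.** A reader might infer that they are assigned unadjusted tests, because "tests will be used if they conform to normal distribution". That sentence concerns continuous variables in general, names no scale and does not say whether raw or change values are compared.

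**Conclusion.** The point holds in a limited form. For a primary outcome, the article fixes a method that sets baseline beside the outcome visits, leaves the tested term open and does not target the comparison behind the sample size.

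- Under the main-effect reading, a lasting 3.5 mm Hg is estimated as 2.33 mm Hg, and power falls from 78% to 21% as the assumed correlation rises from 0.3 to 0.8.
- Under the interaction reading there is no dilution. The test has 74% power (61% if half the effect persists) and does not itself give a difference at either visit.
- The baseline-adjusted week-6 contrast has 88% to 75%, above both readings throughout the range, though only just above the interaction when correlation is high and the effect persists.

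These figures rest on compound symmetry, 9.9 as the SD of change and 102 per arm; the correlation range is assumed. No inflation of type I error is alleged. The change is one that should be made, because it costs almost nothing and recovers some of the power that the stated two-sided inputs lack.

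**What to change.** Replace the repeated-measures ANOVA of ambulatory pressure with ANCOVA or a mixed model for the post-baseline 24-hour systolic values. Include baseline 24-hour systolic pressure, centre, group, visit and group-by-visit. Name the adjusted group difference at week 6 as the primary estimate and report the adjusted difference at week 4 after treatment beside it, each with a 95% CI.

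Include centre because it is the randomisation stratum; expect a gain of only about 0 to 3 power points if it explains 0 to 10% of the variance.

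Do not extend this to the in-office readings by using one first-session value as baseline for all of them. Those readings surround each needling session, and a single fixed baseline would mix the immediate effect with the cumulative one.

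The cost is analysis wording. Baseline pressure is already measured and centre is known from randomisation. The article reports 27 participants recruited and no data analysed, so at that stage the change could be made before any result was known.
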